**Figure 1 F1:**
[figure not shown]
Case series design outline. Key: grey, baseline; green, intervention; blue, follow-up.

### Patient and public involvement

A planning group of public and patient representatives, including people with ADHD (adults (n=5) and children (n=9)), parents of children with ADHD (n=12), school staff (n=9), and education and health psychologists (n=4) has been established to co-create the intervention. Input from this planning group has already extensively informed the design of the intervention and study, refining research questions, selecting outcome measures and considering participant burden. The group will also shape study dissemination plans. The planning group contains around 25 people, and will be consulted throughout the course of the study to make decisions about necessary modifications to the intervention, delivery or research design of a future evaluation. In relation to the study objectives, co-developing the intervention with key stakeholders in the planning group increases the chances of the toolkit being feasible and acceptable in the Primary school context. The group will actively collaborate to refine the toolkit in response to participant feedback to achieve the first aim. They will be consulted as to whether the feasibility study results indicate that a future trial is feasible, in relation to understanding the core features of a high-quality trial. The role of the planning group in co-production of the toolkit is outlined in further detail in the online supplemental material.

10.1136/bmjopen-2022-065176.supp1Supplementary data

Regarding the secondary objectives, the planning group will use data collected to agree on the final primary outcome for a future definitive trial, as well as judge whether trialled measures are suitable measures to assess ADHD symptoms, academic attainment, and child and teacher well-being. The planning group will contribute to the development of the costing framework and evaluate findings from study participants. Finally, the planning group will discuss the findings from observational measures in relation to the toolkit use, helping to understand why any emerging patterns in the data are seen.

### Recruitment and participants

Eight Primary schools, associated school staff and up to 32 children with impairing traits of ADHD (minimum 16 children) will participate in the study, and use the toolkit. All schools and all child participants will receive the intervention. Baseline data regarding treatment as usual will be collected in order to assess normal fluctuations in symptoms and response to any school-implemented treatment as usual during the baseline phase. Baseline data will not be used to exclude participants who have unstable profiles, rather to greater understand the nature of symptom and impairment fluctuation over time.

Recruitment will be through opportunistic sampling, using existing contacts from the planning group such as local Educational Psychology teams, and other education networks in the South West. At the time of writing, four schools have consented to participate and, given the demand for support managing children with ADHD in school, we anticipate no problems recruiting a total of eight schools. This sample of eight mainstream primary schools in the South West of England will allow sufficient variety to purposively sample schools to include a minimum of four in areas of high socioeconomic disadvantage, based on the selection of schools with an index of multiple deprivation above the regional mean. The intervention needs to be able to respond to the range of children with traits of ADHD, including those who are often unrecognised or less likely to access other support, such as girls,^28^ therefore eligible schools will have at least one female pupil meeting eligibility criteria and we will aim to recruit a diverse sample of children with differing ethnicities. A sample of eight schools also allows for the intervention periods to be staggered across the study and successive iterations of the toolkit. All participating schools will use the toolkit in the study for one school term.

Study participants include the school’s senior leadership or head teacher, who will consent to schools’ participation; the school special educational needs (and disabilities) coordinator (SENCo), teachers and teaching assistants (TAs) working with eligible children, eligible children with impairing traits of ADHD, and their parents. Consent will be obtained by a member of the research team through meeting with potential participants face to face or online.

#### School and school staff consent

Each school’s senior leadership team will consent to the school’s participation. They will nominate a mental health lead, who is likely to be the SENCo (as children with ADHD and associated difficulties currently fall under their remit in the UK) and will be referred to as such henceforth. Decisions around recruitment and eligibility criteria have been made in close consultation with the study planning group.

As part of the condition of each school’s participation, the senior leadership team will be asked to ensure that the SENCo and potentially eligible teachers and TAs (those working with recruited children) are supportive of and potentially willing to take part in the study.

#### Identification and recruitment of eligible children and families

Eligible children will either have a clinical diagnosis of ADHD (as reported by the school or parents), or high symptom levels and will be aged 4–10 years (school years Reception-5) at the first baseline assessment to ensure they will be in primary school for the study duration. Children with ADHD may either have not yet received a formal diagnosis, or their family may not wish to pursue a diagnosis, therefore, children with high symptom levels will be eligible. There are no additional exclusion criteria. Teachers and SENCos will identify students who meet criteria for this indicated group using the Strengths and Difficulties Questionnaire Hyperactivity-Inattention Subscale and the impact supplement.^29^ Teachers of potentially eligible children will be asked by the SENCo to complete this brief screening measure, and if this indicates that a child may have probable ADHD (teacher-reported symptoms being ≥6 and impact ≥1), their parent will also be asked to complete the screen in order to ensure that impairments are noted across more than one setting.^2 30^ Should these combined ratings indicate ‘probable’ ADHD according to the validated algorithm, the child will be eligible for inclusion in the study. Probable ADHD is assigned if the parent-report hyperactivity/inattention score is ≥7 and an impact score of 2 is given, or if the hyperactivity/inattention score is ≥9 and an impact score of at least 1 is reported, and the teacher criteria above are met (see sdqinfo.org for syntax).

SENCos will make initial contact with parents of children to clarify eligibility, to provide the study information and to establish whether families are interested in participation in principle. Willing families will be asked to consent to having their details passed to the research team, who will obtain written informed consent from parents and assent from children to participate. Children will be informed of the broad purpose of the research through an age-appropriate information sheet and assent form, unless their parents request otherwise. Should an individual child not meet eligibility criteria but their parents and teacher feel they would benefit from participation, this will be considered on a case-by-case basis. As the intervention is embedded as part of usual school practice, the planning group has indicated that ongoing assent should then be assumed for children through data collection unless the child indicates distress or reluctance.

### Sample size

The planning group has advised that to minimise burden of data collection on teachers, each class teacher should have a maximum of one child participant however this may be revised during the course of the study; for example, if a school feels strongly that several children in one class may benefit, or if two eligible children in the same class also have TA support and the teacher wishes both to participate. Estimating that each of the eight participating schools will have 2–4 participating children and teachers, there will be a total of 16–32 child participants, 16–64 parents, and 16–64 teachers and TAs along with eight SENCos. The total sample size will depend on the distribution of participating parents, teachers and TAs and the distribution of eligible children across different classes within schools: table 1 indicates the minimum and maximum sample sizes.

**Table 1 T1:** Sample size minimum and maximum

Participant type	Minimum number	Maximum number*
School	6	8
Children	16	32
Parents or carers	16	64 (ie, 2 parents per child)
SENCos	8	8
Teachers	16	32
TAs	0	32

*Maximum number based on every eligible school recruiting four pupils, each of which have a different class teacher. We anticipate actual numbers of TAs will be lower than the maximum.

SENCo, special educational needs (and disabilities) coordinator; TA, teaching assistant.

Given that the aim of the study is not to assess effectiveness or efficacy, the potential for the intervention to change between participants, and the case-series design, this study will not be powered to conduct a conventional between-individuals analysis. Instead, we will use multiple individual measurement points to analyse within-individual change and assess whether this replicates (at a descriptive level) across individuals. The pragmatic choice of eight schools allows for this purposive sampling, and both the minimum and maximum sample size of children is sufficient to address our objectives. Based on the mean number of children in eligible year groups in Devon schools, and a conservative estimate of prevalence of ADHD in this age group of approximately 3%, it is expected that each school will have four to eight eligible children, of whom we hope to recruit at least 50%. The recruitment target is feasible: school staff have indicated that a toolkit for ADHD would be perceived as useful and not burdensome as they believe it would be beneficial to their wider classroom management (the planning group highlight the data collection burden as being the reason that teachers should only have one participating student per class).

An established set of study progression criteria are shown in table 2 and will be used to assess success in terms of meeting the study aims. Criteria relate to the recruitment of schools (five or more being acceptable), recruitment of parents and teachers, and completion of study measures as well as some basic metrics of fidelity. The criteria will be reviewed throughout the study, and where individual criteria are Amber or Red, a core academics team meeting and a planning group meeting will be held to discuss, agree and then implement modifications to the study procedure or content.

**Table 2 T2:** Study progression criteria

	Green: acceptable	Amber: discuss, modify	Red: redesign	Assessing
Recruitment of schools	6 or more	5	4 or fewer	Feasibility
Recruitment: teachers, children, parents (considered as separate groups)	>65%	20%–65%	<20%	Feasibility
Retention of schools, teachers, children and parents in study	>65%	40%–65%	<40%	Feasibility
Training completed (teachers)	>90%	70%–90%	<70%	Acceptability and feasibility
Introductory video watched (parents)	>50%	20%–50%	<20%	Acceptability
Child strengths activity completed	>50%	20%–50%	<20%	Acceptability
Adherence to digital Daily Report Card	>70%	50%–70%	<50%	Acceptability
Teacher-completed measures	>70%	50%–70%	<50%	Feasibility
Parent-completed measures	>50%	20%–50%	<20%	Feasibility
Child-completed measures	> 70%	50%–70%	<50%	Feasibility
Observational measures	>70%	50%–70%	<50%	Feasibility
Attendance at toolkit-related meetings	>75%	40%–75%	<40%	Acceptability
Percentage of occasions toolkit reportedly used as instructed	>75%	50%–75%	<50%	Acceptability and feasibility
Follow-up qualitative data collection completed (for each type of respondent: school staff, parents, child)	>50%	20%–50%	N/A	Feasibility

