## Methods and analysis

### Design

A randomised iterative mixed-methods case-series design will be used. Schools will be the units of randomisation, and will be randomised to the time (school term) when they will use the toolkit. The toolkit will be refined after each school has used it for one term, or more frequently if major issues are highlighted during a school’s use of the toolkit. Small, theory-based and data-driven changes hypothesised to be relevant across the school context will be made, as well as reactive changes addressing barriers to implementation. Randomisation to using the toolkit in different school terms allows for inferences to be made as to whether the intervention is improving outcomes, with consistent improvement following the introduction of the core components enabling researchers to potentially rule out alternative explanations for behaviour change, such as improvement due to other support in place or differences in behaviour across the school year. If baseline symptoms and functioning remain on stable trajectories for children across schools, changing only when the intervention is introduced, this implies it is the intervention rather than an alternate factor stimulating the change. It is a commonly used design for single-subject analyses where the intervention cannot be withdrawn and re-implemented such as in an ABAB design.^25–27^

Eight schools will participate in total in two recruitment cohorts of four (in order to avoid later participating schools having to sign up to the study years in advance); each cohort will enter the study at a different time. Schools in each cohort will then be randomly assigned their individual baseline term in the study using a computerised random sequence generator (see figure 1). The length of the baseline period will be the same for each school (one school term), with schools within each cohort entering their baseline period in different school terms; the term in which the intervention is delivered is therefore staggered across the study (figure 1). This design will allow for refining and adapting the toolkit and its implementation based on ongoing participant feedback, maximising the chances it has of being acceptable and feasible (and therefore suitable for further evaluation in a pilot and then definitive cluster randomised controlled trial) by the end of the study.

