#### Aim 2: To establish whether a future trial of effectiveness is feasible

Data on the research process and participant compliance will be evaluated. The quantitative data on recruitment and retention of participants, completion of measures by each participant group (parents, child, teacher, observed) and adherence to the intervention protocol will be assessed relative to the relevant progression criteria described in table 2. These have been informed by existing school-based trials.^48 49^ As above, qualitative findings from the process evaluation and toolkit iteration feedback will be integrated to explain quantitative findings. Should all relevant progression criteria be rated ‘green’, a future trial of ef will be considered feasible. Should criteria be amber or red as the study progresses, potential mitigating modifications will be discussed, such as removing the requirement for parents to actively engage with the toolkit.

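### The school-recruitment criterion is a bare count, so Green shows the study reached its own minimum size and not what share of approached schools would join a larger trial

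*Protocol article*

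**What the plan says.** The protocol article sets the rule out in full in Table 2 (Sample size section). The school row reads "Recruitment of schools 6 or more 5 4 or fewer" for Green, Amber and Red, and is labelled as assessing feasibility. The next row, "Recruitment: teachers, children, parents (considered as separate groups", is banded by percentage (>65%, 20%-65%, <20%), and so is retention.

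The sentence introducing the table describes the school criterion differently: "Criteria relate to the recruitment of schools (five or more being acceptable), recruitment of parents and teachers". Table 2 makes five Amber.

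On supply of schools:
- Design: "Eight schools will participate in total in two recruitment cohorts of four". Table 1 gives a minimum of 6 and a maximum of 8.
- Recruitment and participants: "Recruitment will be through opportunistic sampling, using existing contacts from the planning group", together with other education networks in the South West. In the same section: "At the time of writing, four schools have consented to participate".
- School and school staff consent: "As part of the condition of each school’s participation, the senior leadership team will be asked to ensure" that the SENCo and relevant teachers and teaching assistants support the study and may be willing to join.

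On use of the rating, the Aim 2 analysis section begins its decision rule with "Should all relevant progression criteria be rated ‘green" and concludes that a future effectiveness trial will then be considered feasible. The Design section names a pilot and then a definitive cluster randomised trial as the next steps.

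**The concern.** The school row has one input, the number of schools that signed up. How many were approached or declined does not enter. In a cluster trial the school is the unit recruited, and the share of approached schools that join determines how many must be contacted, over what area and for how long. A criterion labelled feasibility of recruitment ought to bear on that share.

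As written, the row confirms that the study reached the minimum size in its own Table 1. That is useful to know, but it is a different fact from uptake, and the Aim 2 rule treats a Green here as part of the evidence that a larger trial could be run. High and very low uptake earn the same rating.

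**Working it through.** **Inputs from the article.** Green threshold 6, Amber 5, Red 4 or fewer (Table 2). Target 8 schools (Design). Minimum 6 (Table 1). Already consented 4 (Recruitment and participants). No derivation is given for the threshold of 6, so there is no figure to reproduce. Against the target, 6/8 = 75%, but that is progress to target, not uptake.

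**Inputs that are assumptions.** Uptake p and the number of further schools approached N. The article states neither, so ranges are shown. Approaches are treated as independent with a common p.

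**Step 1: what remains to reach Green.** 6 − 4 = 2 further schools. On the text's wording (five or more acceptable) it would be 5 − 4 = 1.

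**Step 2: chance of Green from here.** P(Green) = P(Binomial(N, p) ≥ 2) = 1 − (1−p)^N − N·p·(1−p)^(N−1).

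Example, p = 0.10 and N = 20: 1 − 0.122 − 0.270 = 0.61.

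| Assumed uptake | N = 20 | N = 40 | N = 60 |
|---|---|---|---|
| 5% | 0.26 | 0.60 | 0.81 |
| 10% | 0.61 | 0.92 | 0.99 |
| 20% | 0.93 | 0.999 | 1.00 |

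Further approaches needed for a 90% chance of Green: 77 at 5% uptake, 38 at 10%, 18 at 20%, 12 at 30%, 7 at 50%, 4 at 75%. The rating thus depends on the effort put into approaching schools as well as on their willingness.

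**Step 3: what one Green result could mean.** Uptake = 6/n for n schools approached in total, with exact (Clopper-Pearson) 95% intervals:

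| Schools approached | Uptake | 95% CI | Table 2 rating |
|---|---|---|---|
| 8 | 75% | 35-97% | Green |
| 12 | 50% | 21-79% | Green |
| 20 | 30% | 12-54% | Green |
| 40 | 15% | 6-30% | Green |
| 80 | 7.5% | 3-16% | Green |
| 120 | 5% | 2-11% | Green |

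**Step 4: consequence for a later trial.** For an assumed trial of 40 schools, approaches needed = 40/p: 50 at 80% uptake, 200 at 20%, 800 at 5%. The size of 40 is illustrative; the article gives none.

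**The case against.** The best case for the plan is that the count is a sensible delivery criterion. It fits the target of eight and the range in Table 1, it is one row among many, qualitative findings are integrated under Aim 2, the planning group is consulted on feasibility, and a pilot would precede any definitive trial. A log of approaches may exist in a fuller document. All of that stands, and the absence of a log from the article is not the complaint. What remains is that the article states the rating rule completely, the rule does not use approaches, and the qualitative data described come from participants, not from schools that declined.

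Three stronger readings are tempting, and the documents do not support them.

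- A reader might infer that Green is assured however unwilling schools are. It is not. At 5% uptake and 20 further approaches the chance is 0.26. The South West pool, the requirement for at least one eligible girl per school, the minimum of four schools in disadvantaged areas, and the dates (September 2022 to January 2025) all set a practical ceiling, though the article does not quantify it. Nothing says that 40 or 60 more schools would be approached.
- A reader might infer that unwilling staff are invisible in both the school row and the teacher row, because the entry condition removes their schools before counting. The text says only that leadership will be asked to ensure support and potential willingness. Individual refusal stays possible, and teachers have their own recruitment and retention ratings. Pre-screening is a possibility to be recorded, not an established fact.
- A reader might want the neighbouring >65% / 20%-65% / <20% bands applied to schools. Those bands were set for other groups, and about eight schools cannot support them: even 8/8 has an exact lower limit of 0.025^(1/8) = 63%, below the 65% line. Uptake among existing contacts could also be raised by approaching only likely joiners.

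**Conclusion.** The point holds in a limited form. The school row, as fixed in Table 2, measures delivery to the study's own minimum size and carries no information on uptake, yet it counts towards the Aim 2 conclusion. This follows from the wording of the rule and needs no assumption. Its size does need assumptions: the same Green is compatible with 75% uptake (6 of 8) or 5% (6 of 120), and with four schools in hand a 90% chance of Green takes anywhere from 4 further approaches at 75% uptake to 77 at 5%. How many schools were or will be approached is not stated.

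The limitation attaches to this row. It does not show that the study as a whole can say nothing about recruiting schools, nor that school recruitment will be poor. The conflict between the text (five acceptable) and the table (five Amber) is a separate, plain inconsistency in the same criterion and needs correcting in any case.

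**What to change.** 1. Keep the count as a delivery target, and reconcile the introductory sentence with Table 2 so that one threshold applies.
2. Log every eligible school approached in both cohorts, including the approaches that produced the four schools already consented. Record reasons for declining, with lack of staff support as one category, so that any pre-screening through the entry condition can be seen.
3. Require school uptake (consenting divided by approached), with its exact confidence interval, to be considered in the Aim 2 verdict. State that Green on the count alone does not support feasibility of school recruitment.
4. If the sponsor wants an uptake band, set and justify one for schools; do not copy the teacher, child and parent row.
5. Report uptake with two caveats: the schools come largely through existing contacts, and the sample is small (6/8 has a 95% CI of 35-97%).

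The cost is a recruitment log, one reworded row and one added sentence under Aim 2. Criteria are already to be reviewed throughout the study, so the change can be made while it runs. The downsides are that the picture may be less favourable than the count suggests and that earlier approaches must be reconstructed, perhaps incompletely.

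### The text calls five schools acceptable where Table 2 makes five Amber, and Table 1's minima rest on two different school counts

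*Protocol article*

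**What the plan says.** All the passages are in the protocol article.

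**Threshold for school recruitment.** The Sample size section says that the progression criteria in Table 2 will be used to judge whether the study has met its aims. It then summarises them: "Criteria relate to the recruitment of schools (five or more being acceptable". The first row of Table 2 reads "Recruitment of schools 6 or more 5 4 or fewer", under columns headed "Green: acceptable", "Amber: discuss, modify" and, for Red, redesign. The row is classed as assessing feasibility. The same section says that "where individual criteria are Amber or Red, a core academics team meeting and a planning group meeting will be held" so that modifications can be agreed and made. Under Aim 2 of the Analysis section, a future trial is considered feasible on this condition: "Should all relevant progression criteria be rated ‘green".

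**Minimum sample.** The Sample size text begins "Estimating that each of the eight participating schools will have 2–4 participating children and teachers" and arrives at 16 to 32 children and eight SENCos. Table 1 gives these minima: 6 schools, 16 children, 16 parents or carers, 8 SENCos, 16 teachers and 0 teaching assistants. The section on school and staff consent has each school nominate one lead, expected to be the SENCo. The Sample size section also states that both the minimum and the maximum number of children are enough for the objectives.

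**The concern.** The progression criteria are this study's main prespecified decision tool. It is deliberately not powered, and its conclusion on whether a definitive trial is feasible depends on every relevant criterion being Green. The same word, acceptable, is attached to two different cut-offs for one criterion. If exactly five schools join, someone could choose between them after the count is known. Five is not a remote outcome: the plan is for eight, and the section on recruitment and participants reports four consented at the time of writing.

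The Table 1 point is smaller. A table of minima should describe a study that could occur as listed. Here the school row and the SENCo row appear to assume different numbers of schools. A reader also cannot tell whether 16 children is a floor that holds whatever the number of schools, or simply what eight schools yield at two each. The statement that the minimum sample suffices refers to that figure.

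**Working it through.** **1. The two school-recruitment rules side by side**

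Inputs: the parenthesis in the Sample size text (acceptable if 5 or more) and the Table 2 row (Green 6 or more, Amber 5, Red 4 or fewer).

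| Schools recruited | Sample size text | Table 2 |
|---|---|---|
| 4 | not acceptable | Red |
| 5 | acceptable | Amber |
| 6 | acceptable | Green |

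The rules agree at four or fewer and at six or more. They differ only at five. At five, Table 2 calls for the two meetings and for modifications, and a criterion left at Amber does not satisfy the all-green condition under Aim 2.

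**2. The plan's own sample range, reproduced**

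Inputs: eight schools and 2 to 4 children per school (Sample size text); one SENCo per school (the consent section's single nominated lead, and eight SENCos counted for eight schools).

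- Children: 8 × 2 = 16 and 8 × 4 = 32. Both match the text and Table 1.
- Parents, maximum: 32 × 2 = 64. This matches.
- SENCos: 8 × 1 = 8. This matches.

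So every one of these figures reproduces on a base of eight schools.

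**3. The same formulas at Table 1's minimum of six schools**

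| Quantity | Formula | Result | Table 1 minimum |
|---|---|---|---|
| SENCos | 6 × 1 | 6 | 8 |
| Children, at the floor of 2 per school | 6 × 2 | 12 | 16 |
| Teachers, at one per child | 12 × 1 | 12 | 16 |
| Parents, at one per child | 12 × 1 | 12 | 16 |

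At the ceiling of 4 per school, six schools give 6 × 4 = 24 children, so the range is 12 to 24. Reaching 16 children needs 16 / 6 = 2.67 per school on average, which lies within the stated 2 to 4.

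The SENCo row therefore does not fit the school row at one SENCo per school. The child, parent and teacher rows can be met with six schools, but they were derived from eight.

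**The case against.** The best defence on the threshold is that the operative rule can be identified. The Sample size section says that success will be assessed by the criteria in Table 2, and Aim 2 also points to that table. The conflicting words are a parenthesis in a sentence summarising the table, and they matter at one value only. This stands, and it is why the repair should go to the parenthesis. It does not remove the contradiction: no other passage reconciles the two, and Table 2 gives the label acceptable to Green alone, so the parenthesis cannot be read as meaning merely not Red.

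On Table 1, the minima need not all occur together, and the section on recruitment and participants states 16 children as a minimum in its own right. That also stands for the children, parents and teachers. It helps the SENCo row less. The consent section does not rule out more than one SENCo in a school, but the text counts eight for eight schools.

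Three stronger readings are tempting, and the documents do not support them:

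- A reader might infer that five schools would send the study to redesign. In Table 2 redesign is the Red label; five is Amber, which means discuss and modify.
- A reader might infer that six schools cannot supply 16 children, so that the sufficiency statement is false. Six schools can supply them at 2.67 each. What is missing is a guarantee at the floor of two.
- A reader might set the retention row against the recruitment row, because keeping four of six schools (4/6 = 66.7%, above 65%) is Green while recruiting four is Red. One is a proportion retained and the other a count enrolled. The protocol nowhere requires retained schools to meet the recruitment count, so this is no inconsistency.

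**Conclusion.** The concern holds in two limited parts.

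First, the school-recruitment threshold is contradictory within one section. The effect is confined to exactly five schools, where the verdict moves between acceptable and Amber and, with it, whether this criterion satisfies the all-green condition for a future trial.

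Second, Table 1 mixes two bases. Its minimum of 6 schools conflicts with its minimum of 8 SENCos, a gap of two, on the assumption of one SENCo per school that the protocol implies but does not state as a rule. Its minima of 16 children, parents and teachers rest on eight schools at two each. With six schools the guaranteed number of children is 12, four short, if every school recruits at the floor of two. This is a mismatch of derivation and does not show that 16 is out of reach.

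No inferential result depends on these figures, since the study is not powered. The first part deserves correction because it touches a decision rule; the second is a matter of clear reporting.

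**What to change.** 1. Change the parenthesis in the Sample size section to agree with Table 2: six or more schools acceptable, five Amber. The protocol already makes Table 2 the operative rule, so no criterion changes. Cost: one phrase.

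2. In Table 1, put the school and SENCo minima on one school count, either 6 and 6 or 8 and 8. Cost: one cell.

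3. If the minimum of 6 schools is kept, choose one of two courses:
   - State that 16 children is a separate floor and that six schools would need on average about 2.7 children each to reach it. Cost: one sentence, with the minima for children, parents and teachers unchanged.
   - Restate the minimum, which would be 12 at two per school, together with the sentence claiming that the minimum is sufficient. This costs more than a table edit. The figure of 16 also stands in the Abstract, the section on recruitment and participants and the Sample size text, and 12 children would need its own justification.

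   If the minimum is set at 8 schools, the present figures for children, parents and teachers already fit, and step 3 falls away.
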